### Statistical Analysis

The statistical analysis will be performed at the end of the study. It will involve various tests to evaluate both within-group and between-group efficacy of Navak Guggulu and Vachaharidradi Gana Vati in managing Sthaulya (overweight) among children. For normally distributed continuous variables like BMI, WHR, and skinfold thickness, paired 2-tailed *t* tests will be used to evaluate the efficacy of each intervention within the same group (pre- and posttreatment comparisons).

For nonnormally distributed data, the Wilcoxon signed rank test will be used. For normally distributed data, independent 2-tailed *t* tests will be used for between-group comparisons of mean changes; for nonnormal data, the Mann-Whitney *U* test will be used.

To ensure valid comparisons, the analysis of covariance will be used to account for any potential baseline variations between groups. To evaluate residual efficacy after treatment discontinuation at 180 days, repeated measures ANOVA will analyze longitudinal changes in outcomes, while mixed-effects models will handle missing data or variability across time points. For stratified analysis based on Desha (geography), Kala (season), and Prakruti (body constitution), multivariate regression analysis will identify predictors of treatment efficacy, and interaction analysis will explore the influence of these factors. A statistician consultation will be considered for the selection of the proper statistical method.

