### Hypotheses

The hypotheses are as follows:

H0 null hypothesis: Vachaharidradi Gana Vati and Navak Guggulu along with diet restrictions and Suryanamaskara are not equivalent in efficacy in reducing the BMI in children.H1 alternate hypothesis: The efficacy of Vachaharidradi Gana Vati is equal to Navak Guggulu along with diet restrictions and Suryanamaskara in reducing the BMI in children.

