## Methods

### Study Design

A randomized, standard-controlled, double-blind equivalence clinical trial will be performed. The study flow is depicted in Figure 1. The study participants required for the trial include children with overweight aged between 10 and 16 years of age will be selected from the Outpatient Department and Inpatient Department of the Department of Kaumarbhritya, Mahatma Gandhi Ayurveda College Hospital and Research Centre, Salod (H), and Chhatrapati Shahu Maharaj Shikshan Sanstha’s (CSMSS) Ayurved College and Hospital, Chhatrapati Sambhajinagar, based on the inclusion criteria.

Overweight (Sthaulya) children will be diagnosed as having a BMI greater than or equal to 23 and less than 27 kg/m^2^ [11]. Screening will include hemoglobin percentage, thyroid-stimulating hormone, and random blood sugar. A total of 88 diagnosed children with overweight will be selected after obtaining written informed consent from their guardians. Participants will be randomly divided into 2 groups by block randomization using a computerized random number generator or statistical software. Group A (control group) will receive Navak Guggulu, while group B (trial group) will receive Vachaharidradi Gana Vati orally (Table 1). Medications will be dispensed in opaque containers following the sequentially numbered, opaque, sealed envelope (SNOSE) technique to maintain allocation concealment. Both groups will receive counseling to perform 12 Suryanamaskara (Sun Salutation) per day and adhere to the dietary restrictions. Guardians will be educated and advised to support their children’s consistent participation in the interventions. All the baseline parameters will be recorded at the study’s initiation. The treatment duration will be 90 days, with follow-up assessments on the 15th, 30th, 45th, 60th, 75th, and 90th day to monitor progress and ensure adherence. Lipid profile will be assessed before treatment and on the 90th day of intervention to evaluate the efficacy of the interventions. An additional follow-up will occur on the 180th day to determine whether the intervention’s possible effects are lasting.

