### Justification on the Formula

The equivalence formula for parallel-group design is particularly suitable for this study, as it is specifically designed to determine the sample size needed to assess whether 2 interventions—Vachaharidradi Gana Vati and Navak Guggulu—are statistically equivalent within a defined margin of clinical acceptability. This approach is crucial for trials aimed at establishing equivalence rather than superiority or noninferiority. The formula accounts for the population variability in the population by incorporating the SD of the control drug and ensures a robust comparison by considering both type I and type II error rates, set at 5% and 20%, respectively. This balance between the risks of false-positive and false-negative results is critical in equivalence trials, where even small differences may have clinical significance.

By including the true difference in means (δ), the formula ensures that the calculated sample size is adequate to detect equivalence within the predefined margin. The adjustment for a 2-tailed test reflects the bidirectional nature of equivalence testing, ensuring that the study is powered to detect differences in either direction. Given these attributes, this formula provides a scientifically robust framework for calculating the required sample size, ensuring that the study’s conclusions about equivalence are statistically valid and clinically meaningful. The sample size ensures that each participant receives individualized care and monitoring.

For reference values, a clinical trial paper was used [44].

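### The named between-group tests have no difference as their null, the reverse of the stated equivalence null, and no stated analysis compares an estimate with a margin

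*Protocol article*

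**What the plan says.** The commitment to equivalence is explicit. Study Design: "A randomized, standard-controlled, double-blind equivalence clinical trial will be performed". Under Hypotheses, the null is that the two regimens "are not equivalent in efficacy in reducing the BMI in children", and the alternative is "The efficacy of Vachaharidradi Gana Vati is equal to Navak Guggulu". Justification on the Formula adds that "the formula ensures that the calculated sample size is adequate to detect equivalence within the predefined margin".

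The Statistical Analysis section then names the methods:

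- Between-group change, normal data: independent 2-tailed t "tests will be used for between-group comparisons of mean changes".
- Between-group change, non-normal data: "for nonnormal data, the Mann-Whitney" U test.
- Baseline imbalance: "the analysis of covariance will be used to account for any potential baseline variations between groups".
- Residual efficacy at day 180: repeated measures ANOVA, with mixed-effects models for missing data or variability over time.

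The section ends by saying that consulting a statistician on the choice of method will be considered. It contains no two one-sided tests, no confidence interval set against a margin, and no rule for declaring equivalence. A margin is called predefined, but no number is given that name. The Participants section defines the 0.57 in the sample size formula as the true difference in means.

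**The concern.** An equivalence trial has to reject the hypothesis that the treatments differ by at least the margin. The t and Mann-Whitney tests start from the opposite null. If either is significant, it shows a difference. If it is not, the data are compatible with no difference, but they may be equally compatible with a difference that matters. Neither result rejects the null stated under Hypotheses.

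The trial's main claim therefore has no stated analysis behind it. The incentive also points the wrong way: a smaller or noisier data set makes non-significance more likely. The Ethical Considerations section excludes any child who misses a follow-up visit during treatment, so loss of analysed participants is a real possibility.

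**Working it through.** **Inputs.** From the Participants section: SD 0.86, delta 0.57, Z values 1.96 and 0.84, 39 per arm before dropout. From the randomization section: 44 per arm enrolled. Two assumptions are mine: that 0.57 and 0.86 are in kg/m2 of BMI change (the section gives no unit), and that 0.57 is the margin (the section does not say so).

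**The plan's own figure.** 2 × (1.96 + 0.84)² × 0.86² / 0.57² = 35.7, so 36 per arm, not the printed 39. That is a separate error. The printed expression with these Z values is the one for detecting a difference. An equivalence calculation with margin 0.57, one-sided 5%, 80% power and zero true difference uses 1.645 + 1.282 instead: 2 × 2.927² × 0.86² / 0.57² = 39.0. So 39 agrees with a margin of 0.57, but 35.7 × 1.1 = 39.3 is near it too, and the agreement does not show that 0.57 was meant as the margin.

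**Setting the nulls side by side.**

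| Source | Null | Rejecting the null shows |
|---|---|---|
| Hypotheses section | not equivalent | equivalence |
| t test, Mann-Whitney U | no difference | a difference |
| Two one-sided tests | absolute difference at or above the margin | equivalence within the margin |

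**Error if non-significance were read as equivalence.** Standard error = 0.86 × √(2/n). With a true difference of 0.57, the noncentrality is 0.57 divided by the standard error, and the error is the noncentral t probability between the two-sided 5% critical values.

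| n per arm | SE | Noncentrality | Critical t | P(non-significant) |
|---|---|---|---|---|
| 44 | 0.183 | 3.11 | 1.988 | 13.3% |
| 39 | 0.195 | 2.93 | 1.992 | 17.6% |
| 30 (illustrative) | 0.222 | 2.57 | 2.002 | 28.6% |

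**Two one-sided tests at 5%** (90% interval inside ±0.57). The error at a true difference of 0.57 is 5.0% at each of these sizes. Power at zero true difference is approximately 2Φ(0.57/SE − 1.645) − 1, which gives 80% at 39 and 86% at 44. The exact t-based values are 79% and 85%.

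**One possible result.** With 44 per arm, SD 0.86 and an observed difference of 0.35, the 95% interval is 0.35 ± 1.988 × 0.183, or −0.01 to 0.71, so the t test is non-significant. The 90% interval is 0.35 ± 1.663 × 0.183, or 0.05 to 0.65, which runs past 0.57. Equivalence is not shown.

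**Sensitivity to the margin** (illustrative margins, SD 0.86, zero true difference, power of the two one-sided tests):

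| Margin | 39 per arm | 44 per arm |
|---|---|---|
| 0.57 | 79% | 85% |
| 0.50 | 63% | 71% |
| 0.40 | 30% | 40% |

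**The case against.** **This is an analysis plan detail.** The article is condensed and a separate plan may exist, so a missing interval-against-margin rule would not count alone. That is fair. What remains is that the article names specific 2-tailed tests for the between-group comparison, and their null is the reverse of its own. That is a contradiction between two stated items.

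**The methods are not all difference tests.** This stands. ANCOVA and mixed models can yield an adjusted difference with an interval that could be judged against a margin, and the choice of method is left partly open. Repeated measures ANOVA and the mixed models are tied to day 180, a secondary objective. But no step uses an interval this way, no margin has a value, and a consultation that will be considered is not a commitment.

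**A reader might infer that the investigators intend to call a non-significant p value equivalence.** The document says no such thing. It is only the one apparent route that the named tests leave open.

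**A reader might also take the alternative of equal efficacy as a claim of exact equality, which no data could prove.** The justification section explains equivalence as lying within a defined margin, so the wording is loose and is not a second error. Nor are rank methods unusable: an ordinary Mann-Whitney p value cannot be set against a margin, but a margin-shifted rank test or a Hodges-Lehmann interval can.

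**Two one-sided tests do not cure poor adherence.** Correct. If adherence shrank a true 0.57 to 0.40 (illustrative), they would declare equivalence at 44 per arm in about 23% of trials. They control the error from noise and small numbers, not from dilution of the contrast.

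**Conclusion.** The point holds in this form: the named t and Mann-Whitney tests do not address the stated null, no planned analysis compares a between-group estimate with a margin, and so no stated analysis can establish equivalence.

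The size is conditional. If the margin is 0.57 kg/m2 and the SD is 0.86, treating non-significance as equivalence carries an error of about 13% with all 44 per arm analysed and about 18% with 39, against about 5% for two one-sided tests. The 29% at 30 per arm only shows the direction as data are lost. A different margin or SD changes these figures, but the mismatch of hypotheses depends on neither.

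**What to change.** 1. Restate the null as an absolute difference in mean BMI change at or above the margin, and the alternative as an absolute difference below it.
2. Name the numeric BMI margin and justify it clinically before unblinding. Say whether the 0.57 used for sizing is that margin.
3. Make the primary between-group analysis the ANCOVA-adjusted difference in mean BMI change. Declare equivalence only if its 90% confidence interval lies wholly within plus or minus the margin (two one-sided tests at 5%).
4. State that a non-significant t or Mann-Whitney test is not evidence of equivalence.

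**Cost.** With a margin of 0.57, only the text of the Hypotheses and Statistical Analysis sections changes. The same 88 children give about 79% power (39 per arm analysed) to 85% (44 per arm) at zero true difference. If a smaller margin is justified, power falls as tabulated, and the protocol should restate it or revise the sample size.

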### Inclusion Criteria

The inclusion criteria are as follows: participants irrespective of gender, religion, and socioeconomic status, age group between 10 and 16 years with signs and symptoms of overweight (Sthaulya) due to exogenous causes, participants with BMI ≥23 and <27 kg/m^2^, and parents who are willing to provide written informed consent for their children to be included in the study.

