### Participants

It is crucial to calculate the effect size according to the equivalence or superiority formula with the help of the SD and mean difference of the reference paper [44]. This approach enhances the RCT, making it superior to other types of research. In this study, an attempt is made to assess the equivalence effect of Vachaharidradi Gana Vati against the standard controlled drug, Navak Guggulu. The equivalence formula is applied, and the sample size is calculated to minimize any bias. So, the formula for equivalence (parallel design) has been used to calculate the sample size of this study. For that, the reference values of the control drug have been used [44].

The formula for equivalence (parallel design) is:

where *Z*_α_=1.96, α=type I error at 5%, σ=SD, *Z*_β_=0.84 (for equivalence 2-tailed), β=type II error at 20%, and δ=true differences in means.

Sample size (N) = *n*1 = 2 × (1.96 + 0.84)^2^ × (0.86)^2^/(0.57)^2^ = 39 each

Total=78 samples. With 10% dropout=43 each=86 samples.

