### Outcomes

#### Primary Outcome—BMI

BMI will be calculated as the ratio of body weight to the square of height (kg/m^2^). Indian Academy of Pediatrics 2015 charts will be used to categorize weight as normal, overweight, and obese.

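### A normality check can switch the primary BMI comparison from a difference in means to a Mann-Whitney test, although the equivalence design is sized on a mean difference and no analysis is given precedence

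*Protocol article*

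**What the plan says.** All references are to the protocol article.

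- **Design and hypothesis.** Study Design: "A randomized, standard-controlled, double-blind equivalence clinical trial will be performed". Under Hypotheses, the null is that the two treatments "are not equivalent in efficacy in reducing the BMI in children". BMI in kg/m^2 is the primary outcome.
- **Sample size.** The Participants section uses an SD of 0.86 and a delta of 0.57, and defines delta as the true mean difference. Justification on the Formula then says that including delta makes the sample size "adequate to detect equivalence within the predefined margin". That margin is given no number.
- **Analysis.** Statistical Analysis sends between-group comparisons of mean changes to an independent two-tailed t test when data are normal, and "for nonnormal data, the Mann-Whitney *U* test will be used". BMI is mentioned only in the within-group sentence, which begins "For normally distributed continuous variables like BMI, WHR, and skinfold thickness". That wording is conditional and does not exempt BMI from the non-normal branch.
- **Other models.** The same section plans ANCOVA to deal with baseline differences between the arms. It also plans repeated-measures ANOVA and mixed-effects models for the question of residual effect at 180 days. None of these is called primary, and no order is set between them, the t test and Mann-Whitney.

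**The concern.** In an equivalence trial the main result is an estimate with an interval, set against a margin on the same scale. Here the hypothesis and sample size concern BMI reduction measured as a difference in means. If the normality check fails, the named between-group test becomes a rank test. It asks whether values in one arm tend to exceed those in the other, and it returns no difference in mean BMI. A non-significant result from it means only that no difference was shown, which is not evidence of equivalence.

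The choice is made by a preliminary test on the trial's own data, and neither the test nor its level is given. Two analysts following the text could reach different primary analyses, one with a result in kg/m^2 and one with a rank-based p value.

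**Working it through.** **1. Is the design set on a mean difference?**

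Inputs from the Participants section: SD 0.86, delta 0.57, Z values 1.96 and 0.84, type I error 5%, type II error 20%, 39 per arm.

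- Expression as printed: 2 × (1.96 + 0.84)² × 0.86² / 0.57² = 2 × 7.84 × 0.7396 / 0.3249 = 35.7, so 36 per arm. This does not reproduce 39.
- Two one-sided tests at 5% each, 80% power, true difference zero, margin 0.57: 2 × (1.645 + 1.282)² × (0.86 / 0.57)² = 38.99, so 39 per arm. This is the stated figure.

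The match supports reading 0.57 as the working equivalence limit, but it is an inference, because the article does not call 0.57 a margin. On either reading, both inputs (SD and delta) are on the scale of a mean. The mismatch between the printed expression and 39 is a separate matter.

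**2. What does each planned between-arm analysis deliver?**

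| Analysis | When used | Mean difference in kg/m^2? | Compared with a margin? |
|---|---|---|---|
| Independent t test | data normal | yes | not stated |
| Mann-Whitney | data not normal | no | not stated |
| ANCOVA | for baseline differences | yes, adjusted | not stated |

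The second row removes the estimate on the design scale, and the third would restore it. Nothing says which row decides if both are reported.

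**3. How often would the switch occur?**

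The article gives no rule, so these are assumptions: Shapiro-Wilk at 5% in each arm, a switch if either arm fails, 44 per arm, and change with SD 0.86, either normal or gamma-shaped.

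- Normal change: by arithmetic 1 − 0.95² = 9.75%; simulated, about 10%.
- Skewness 0.7: about 58%.
- Skewness 1.0: about 87%.

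**4. Is the switch needed to keep the mean-based analysis valid?**

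Standard error with 44 per arm: 0.86 × √(2/44) = 0.183. In the same simulations at skewness 0.7 and 1.0:

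- the mean-based 90% interval covers the true difference in about 90% of trials;
- with the true difference at 0.57, equivalence is wrongly declared in about 5% of trials.

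At this sample size, skewness of that degree does not make the mean-based interval unreliable.

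**5. Could ranks give an answer in kg/m^2?**

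Yes, through a Hodges-Lehmann shift interval, which the article does not plan. With no true difference and skewness 1.0, the 90% shift interval lay within ±0.57 in about 90% of trials, against about 84% for the mean-based interval. It can therefore be somewhat more efficient, but it estimates a shift rather than a difference in means and can lead to a different decision.

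**The case against.** The strongest reply is that the plan does not lose the mean difference. ANCOVA stands outside the normality rule and gives an adjusted difference in kg/m^2 whichever branch applies. This stands, so a reader who infers that the 0.57 figure could not be applied to BMI at all goes too far. What remains is that ANCOVA has no stated precedence.

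Four further replies also limit the point:

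- **0.57 is not labelled a margin.** Correct; see step 1. The point needs only that the sample size is set on a mean difference.
- **Eligibility does not decide the matter.** Because entry is limited to "participants with BMI ≥23 and <27 kg/m^2", a reader might infer that BMI is non-normal by design and that the switch is close to certain. The between-arm comparison is of changes, however. A cut-off on baseline BMI does not make change non-normal, and follow-up BMI is not cut off.
- **Ranks are not worthless.** A reader might infer that the switch gains nothing. Step 5 shows that it can gain efficiency under skewness. The objection is to letting the data choose the estimand, not to rank methods.
- **The t-test branch is no better on equivalence.** True. A two-tailed t test also applies no margin. That is a separate and larger point, and correcting it would still leave the rank branch open.

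**Conclusion.** The point holds as a problem of an unfixed primary analysis. The text lets an undefined normality check decide whether the BMI comparison is a difference in means or a rank test, in a trial whose hypothesis and sample size call for equivalence on the mean scale. The planned ANCOVA lessens the harm but does not remove it, because it is not given precedence.

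The size depends on assumptions that the article does not settle: the normality test, its level, whether it is applied per arm, and the shape of BMI change. Under those in step 3, the switch ranges from about 10% to about 87% of trials. Across that range the mean-based interval keeps close to its nominal coverage and error, so the switch is not needed for validity. The change should be made before the data are unblinded. The documents do not support a claim that the primary question would be left without any answer in kg/m^2.

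**What to change.** For BMI only, remove the normality switch. Name one primary analysis: the between-arm difference in mean BMI change in kg/m^2 from the already planned ANCOVA, adjusted for baseline BMI, with its confidence interval, whatever a normality check shows. Set that interval against the equivalence margin, which the plan should state as a number. Report a bootstrap or rank-based (Hodges-Lehmann) interval as a sensitivity analysis.

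Rank tests may stay for the ordinal symptom grades and for other secondary measures such as lipids. Nothing examined here argues against them there.

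The cost is about one sentence in Statistical Analysis and one additional sensitivity analysis. The sample size does not change. The downside is small: a mean is more sensitive to outlying values and can be somewhat less efficient than ranks when change is skewed (about 84% against 90% of intervals inside ±0.57 at skewness 1.0). The sensitivity analysis would show whether this matters.

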#### Secondary Objectives

The secondary objectives are (1) to evaluate the residual efficacy of Navak Guggulu versus Vachaharidradi Gana Vati in children with Sthaulya (overweight) after discontinuation of treatment after 180 days as well; (2) to study the effect of desha, kala, and prakruti on the children with overweight; and (3) to study the adverse effects of Vachaharidradi Gana Vati if any.

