### Ethical Considerations

The Mahatma Gandhi Ayurved College Hospital and Research Centre’s Institutional Ethics Committee approved this study (registration: MGACHRC/IEC/July-2022/521), and it was also registered with the Clinical Trial Registry of India (CTRI/2023/03/051135). The same ethical committee also approved the addition of the site at CSMSS Ayurved College, Chhatrapati Sambhajinagar. After receiving a No Objection Certificate from the institutional ethical committee of the CSMSS Ayurved College (AMCS/1407/2023), the participant recruitment at both sites will be initiated. The institutional ethical committee will decide on the end point and oversee the trial as it progresses. The researchers will assess any adverse events and will report to the ethics committee. Consent from parents and assent from patients (older than 12 years) will be obtained before conducting the trial in the local language while explaining every aspect of the study. Every participant will get information regarding the study’s design and objectives, data confidentiality, and the freedom to withdraw from the study at any moment without giving a reason. The informed consent form includes a patient information sheet (part 1) and a certificate of consent (part 2). Secondary analysis will be covered without additional consent. Data will be anonymized, and the personal information of the participants will be kept confidential before, during, and after the trial. Physical data will be stored in a protected storage facility, with access available only to the researchers. Computerized data will be held in a password-protected computer. Data access will be restricted to members of the research team only. During data analysis, measures will be taken to protect participants’ privacy. Participation in the study is completely voluntary; hence, no incentive will be provided to the participants. During the treatment period, if the patients’ condition worsens, the case will be excluded and will receive conventional treatment and care until the symptoms subside, free of charge. The ethics committee will be informed of the patient’s condition. The therapy will be discontinued, and the child will be withdrawn from the study if any other illness arises during the treatment period that could influence study outcomes. Similarly, if a participant experiences personal issues that prevent continuation of therapy and are likely to affect the study results, they will also be withdrawn. If the patient misses any of the periodic follow-ups during the intervention, they will be excluded from the study.

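### The day-180 residual-efficacy objective is given two models with no order between them, neither tied to a day-180 between-arm difference, and the missed-visit exclusion removes most of the data the mixed model is meant to handle

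*Protocol article*

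**What the plan says.** The first secondary objective in the protocol article is comparative: "to evaluate the residual efficacy of Navak Guggulu versus Vachaharidradi Gana Vati in children with Sthaulya (overweight) after discontinuation of treatment after 180 days". Under Study Design the on-treatment period has visits "with follow-up assessments on the 15th, 30th, 45th, 60th, 75th, and 90th day", and then "An additional follow-up will occur on the 180th day". With baseline, that makes eight occasions: 15-day steps up to day 90, then a single 90-day gap.

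For this objective the Statistical Analysis section states that "repeated measures ANOVA will analyze longitudinal changes in outcomes, while mixed-effects models will handle missing data or variability across time points". It closes by leaving the choice of method to a possible consultation with a statistician.

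Ethical Considerations adds a rule that bears directly on missing data: "If the patient misses any of the periodic follow-ups during the intervention, they will be excluded from the study".

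Study Design gives diet restriction and Sun Salutation to both arms. Only the tablet differs, and no arm goes without a tablet.

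**The concern.** The objective asks one question: how do the arms differ at day 180, 90 days after the tablets stop? Two models are named for it, and they can disagree. They use different children when data are incomplete, and they produce different quantities unless a common contrast is fixed.

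A standard repeated measures ANOVA gives a time effect, a group effect averaged over visits, and a time-by-group test. None of these is the day-180 difference with an interval. The time effect within an arm is also not a tablet effect, because diet restriction and Sun Salutation run in both arms.

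The two sections also work against each other. One names a model because some children will have missing values. The other excludes children who miss an on-treatment visit, so most of the records that would justify the model may never reach it.

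At stake are which children are analysed for this objective and which number is reported as its answer.

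**Working it through.** The protocol gives no figure for this analysis, so there is none to reproduce. The check has two parts.

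**1. Who is lost, and to which rule**

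Inputs: 44 children per arm (Table 1 of the protocol article); six on-treatment visits and one at day 180 (Study Design). The per-visit missing rate *m* is not in the protocol. I assume 1% to 5%, independent across visits.

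- Left after the missed-visit exclusion, whichever model is used: 44 × (1 − *m*)^6
- Left for an ANOVA that also needs day 180: 44 × (1 − *m*)^7

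| *m* | After exclusion rule | Lost to that rule | Also with day 180 | Extra loss from ANOVA |
|---|---|---|---|---|
| 1% | 41.4 | 2.6 | 41.0 | 0.4 |
| 2% | 39.0 | 5.0 | 38.2 | 0.8 |
| 3% | 36.7 | 7.3 | 35.6 | 1.1 |
| 5% | 32.3 | 11.7 | 30.7 | 1.6 |

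While the exclusion stands, the last column does not depend on how many occasions enter the ANOVA, because every child still in the trial has complete on-treatment data. If the exclusion were lifted and an eight-occasion ANOVA kept, the ANOVA would remove the same children again: 44 − 35.6 = 8.4 per arm at 3%, and 44 − 30.7 = 13.3 at 5%. Day-180 values would by then exist for 44 × 0.97 = 42.7 and 44 × 0.95 = 41.8 per arm. The two changes therefore have to be made together.

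**2. Do the omnibus tests answer the day-180 question?**

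A simulation used 44 per arm, eight occasions, complete data and 4,000 runs. SD 0.86 and difference 0.57 come from the protocol's sample size calculation. Treating 0.86 as the SD of change is an assumption, as are compound symmetry and a correlation of 0.8 between visits. The direct contrast is a *t* test on change from baseline to day 180.

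- *(a) Difference rises linearly to 0.57 at day 90 and is zero at day 180.* Time-by-group is significant in 91% of runs and the group effect in 15%. The direct day-180 contrast is significant in 4.6%, close to its nominal 5%.
- *(b) Difference of 0.57 at day 180 only.* The group effect averages this to 0.57 / 8 = 0.07 and is significant in 6% of runs. Time-by-group is significant in 86% and the direct contrast in 87%.

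In (a) the interaction is right that the profiles differ, but it says nothing about day 180, where they coincide. In (b) the interaction detects that something differs but does not say at which visit or by how much, and the group effect almost loses it. Neither test replaces an estimate at day 180.

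**The case against.** The strongest reply is that the remedy is already half written. The quoted sentence gives the models different roles, and the mixed model can use incomplete children and yield a day-180 contrast. The section also provides independent *t* tests of mean changes and analysis of covariance, neither restricted to day 90. Contrasts after an ANOVA are routine, and their exact form, the covariance structure and any sphericity correction can properly sit in an analysis plan that is not shown. This stands in part: the plan does not lack a suitable method. What remains is that the sentence written for this objective names two models, gives precedence to neither and names no contrast.

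Three stronger readings are tempting and are not supported.

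- *A reader might infer that the ANOVA costs 19% to 30% of the children*, since 0.97^7 = 81% and 0.95^7 = 70%. Six of those seven visits fall under the exclusion rule whichever model is used, and the rates are assumed. The ANOVA's own share is the last column of the table.
- *A reader might infer that a time effect will be reported as lasting tablet efficacy, or a non-significant interaction as lasting equivalence.* The protocol says neither. Its Discussion credits the sustained effect to the combined interventions, and the secondary objective makes no equivalence claim.
- *A reader might infer from scenario (a) that the interaction test misfires.* It does not, because the arms do differ over time there. It answers a different question.

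It can also be said that exclusion from the study need not mean deletion of values already recorded. The protocol does not say, and this is one reason the two sections need reconciling.

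**Conclusion.** The point holds in a limited form. The protocol names two models for a between-arm question at day 180, does not say which one decides it, and ties neither to the day-180 difference. The ANOVA's omnibus tests do not supply that difference. With the exclusion rule in force, the ANOVA's additional loss is small: about 1 to 2 children per arm at an assumed 3% to 5% missed per visit, and fewer at lower rates. The exclusion rule itself accounts for about 7 to 12 per arm at the same rates, and it leaves the mixed model mainly children who miss only day 180.

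The counts rest on assumed, independent missingness and on reading the exclusion as removing the child's data. The simulation rests on the assumed correlation, covariance pattern and SD of change. The unresolved choice of model and the conflict between the two sections rest on the text alone. Because the objective is secondary and a suitable model is already named, this is an improvement worth making and not a threat to the trial's main result.

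**What to change.** 1. Remove repeated measures ANOVA for this objective.
2. Name one mixed model as its analysis: BMI change on baseline BMI, arm, visit as a category, and arm-by-visit, using all available visits of all randomised children.
3. Report the day-180 between-arm difference from that model with its confidence interval as the answer to the residual-efficacy objective.
4. Reconcile Statistical Analysis with Ethical Considerations so that a missed visit does not remove a child's data from the analysis. This concerns the analysis set only and implies no view on when a child's treatment should continue or stop.
5. Describe within-arm change, including day 90 to day 180, as the effect of the combined package of tablet, diet restriction and Sun Salutation.

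The cost is analysis wording. The visits are already scheduled and no new measurement is needed. For a child already excluded, the model uses whatever was recorded up to that point.
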